**Discussion::**

This study will evaluate the effectiveness and safety of bosentan combined with vardenafil in the treatment of pulmonary hypertension after congenital heart disease in children. The results of this experiment will provide a clinical basis for the use of bosentan combined with vardenafil to treat pulmonary hypertension after congenital heart disease in children.

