## Introduction

1

Congenital heart disease (CHD) refers to vascular or heart malformations caused by abnormal growth of cardiac blood vessels during the embryonic period. It is a common cardiovascular disease in pediatrics,^[1]^ due to the large amount of left to right shunts at the defect site of CHD. The blood volume of the pulmonary circulation increases significantly, and the high flow puts the pulmonary blood vessels in a state of high pressure and high resistance, causing pulmonary arterial hypertension. Pulmonary hypertension is one of the common and serious complications of congenital heart disease in children. About 10% of children with congenital heart disease develop into PAH,^[2]^ which can occur at various stages in the evolution of congenital heart disease in children. The surgical effect and prognosis of patients have a direct impact, and the perioperative mortality rate of children with CHD and severe PAH is higher.^[3]^ Therefore, effectively reducing pulmonary hypertension is a key step to improve the surgical efficacy and quality of life of CHD patients.

There are currently 3 types of targeted therapy drugs recommended, including endothelin receptor antagonists, prostaglandin i2, and phosphodiesterase 5 inhibitors (PDE-5 inhibitors).^[4]^ Bosentan is a representative drug of endothelin receptor antagonists, which has the effects of reducing pulmonary vascular resistance, improving hemodynamic indicators, improving exercise tolerance, and improving the patient's survival rates.^[5,6]^ Vardenafil is a highly selective inhibitor of phosphodiesterase-5 (PDE-5), which can selectively inhibit PDE-5 activity and reduce the degradation of cyclic guanosine monophosphate (cGMP). The latter can further activate protein kinase G, increase potassium ion channels, reduce calcium ion concentration, thereby reducing pulmonary artery pressure. At present, clinical studies have pointed out that the two-drug combination therapy can significantly improve the patient's exercise capacity, improve the patient's heart function and relieve the symptoms of dyspnea,^[7]^ but there are too few similar studies, and the sample size is not large, and it is difficult to draw reliable conclusions. Therefore, the purpose of this randomized controlled trial is to evaluate the effectiveness and safety of bosentan combined with vardenafil in the treatment of postoperative pulmonary hypertension in children with congenital heart disease.

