### Sample size

2.3

The calculation of the sample size is based on the results of the 6 MWTD. According to the results of the pre-test, the average score of the experimental group is estimated to be 495.47 and the standard deviation is 54.72. The control group averaged 456.33 and the standard deviation was 54.68. The sample size calculation formula is as follows$$n=n1=n2=\frac{{\left(u_{\alpha }+u_{\beta }\right)}^{2}\times \sigma^{2}}{\delta^{2}}\times 2$$

At the 5% significance level, a total of 34 patients are required for each group to achieve 90% power. The estimated withdrawal rate is 20%, and 42 patients will be included in each group.

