### Observation index

2.7

1.Oxyhemoglobin saturation SpO2, using GEM3000 blood gas analyzer to measure SpO2 before and after treatment in the 2 groups;2.(2) 6-min walking test distance (6 MWTD): For children who can cooperate with walking to walk back and forth in a quiet and airy 30-m corridor, measure the 6-min walking distance;3.The patient uses a SwanGanz floating catheter for right heart catheterization in a resting state to determine systolic pulmonary artery pressure, pulmonary artery pressure, and aortic pressure. Fick method is used to calculate mean pulmonary artery pressure, pulmonary circulation blood flow quantity/systemic circulation Blood flow quantity, pulmonary artery systolic pressure/systemic artery systolic pressure;4.The patient got 5 ml of fasting venous blood in the morning before and after treatment, and the brain natriuretic peptide was measured by enzyme-linked immunosorbent assay;5.Borg score^[9]^ (divided into 0–10 grades, 10 is the most serious, consciously exhausted), cardiac function classification (NYHAFC);^[10]^6.Adverse reactions: including dizziness, headache, facial flushing, abnormal liver, and kidney function, etc.

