### Statistical analysis

2.9

Data were analyzed using the statistical software package SPSS version 25.0 (Chicago, IL). Continuous variables were described as the mean ± standard deviation, and differences between groups were analyzed using a series of one-way analysis of variance (ANOVA) with Bonferroni posthoc test, while differences between groups over time were analyzed using multiway ANOVA with Bonferroni posthoc test. Categorical variables were described as the number (%), and were analyzed by Fisher exact test. A *P* value of <.05 was considered statistically significant.

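### Safety is a stated objective, but the only inferential method fixed for adverse reactions is Fisher's exact test at P<.05, which at 42 per group cannot show how large an excess has been excluded; report risk differences with 95% intervals.

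*Protocol article*

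**What the plan says.** The Introduction of the protocol article gives the aim: "the purpose of this randomized controlled trial is to evaluate the effectiveness and safety of bosentan combined with vardenafil". The Discussion part of the Abstract repeats it: "This study will evaluate the effectiveness and safety of bosentan combined with vardenafil in the treatment of pulmonary hypertension after congenital heart disease in children". It adds that the results are meant to give a clinical basis for using the combination.

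The safety outcome is the last item in section 2.7: "Adverse reactions: including dizziness, headache, facial flushing, abnormal liver, and kidney function, etc". These are counts of children with a reaction.

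Section 2.9 gives one rule for such data: "Categorical variables were described as the number (%), and were analyzed by Fisher exact test". The threshold is a P "value of <.05 was considered statistically significant". Whether the test is one- or two-sided is not stated.

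The size of the trial was set without reference to safety. Section 2.3 says: "The calculation of the sample size is based on the results of the 6 MWTD". It continues: "At the 5% significance level, a total of 34 patients are required for each group to achieve 90% power", and then "The estimated withdrawal rate is 20%, and 42 patients will be included in each group".

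**The concern.** Fisher's exact test asks whether the data are compatible with no difference between the arms. It can flag harm, but it does not say how much harm the data rule out, and that is what a safety objective needs. The trial is small and was sized on another outcome, so a non-significant result for a given reaction is likely even when adding bosentan raises its frequency by 10 or 15 percentage points.

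The P value is the only inferential output fixed for adverse reactions. The percentages reported beside it carry no statement of precision. A reader who wants a clinical basis for use in children would therefore see two percentages and a verdict of significant or not, with no upper limit on the excess.

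**Working it through.** **Inputs from the article**
- Patients per group: 42 enrolled; 34 required before the allowance for withdrawal (section 2.3).
- Walk-distance assumptions: means 495.47 and 456.33, SDs 54.72 and 54.68, 5% level, 90% power (section 2.3).
- Test and threshold: Fisher's exact test, P<.05 (section 2.9).

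**Inputs that are assumed**
- The article gives no adverse-reaction rates, so a range is shown.
- Sidedness is not stated. Two-sided is taken as the usual convention, with one-sided as a check.

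**Step 1: the article's own sample size.** The difference is 495.47 − 456.33 = 39.14. The mean variance is (54.72² + 54.68²)/2 = 2992.1. The stated formula is n = 2(u_α + u_β)²σ²/δ².
- One-sided 5%: 2 × (1.645 + 1.282)² × 2992.1 / 39.14² = 33.5, so 34. This matches.
- Two-sided 5%: 2 × (1.960 + 1.282)² × 2992.1 / 39.14² = 41.0, so 42 after rounding up. This does not match the stated 34.
- Withdrawal: 34 / 0.8 = 42.5; the article states 42.

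The stated 34 reproduces only with a one-sided level, which is why one-sided results are also shown below. No adverse-reaction rate enters this calculation.

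**Step 2: exact chance of missing a harm.** For n per arm, take every pair of counts (i in control, j in treatment). Weight each pair by Bin(i; n, p₀) × Bin(j; n, p₁). Sum the weights where Fisher P<.05 and j>i. The miss rate is 1 minus that sum.

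| Assumed control vs treatment rate | Missed, 42 per group | Missed, 34 per group |
|---|---|---|
| 2% vs 10% | 87% | 93% |
| 5% vs 15% | 80% | 87% |
| 5% vs 20% | 56% | 69% |
| 10% vs 20% | 83% | 88% |
| 10% vs 25% | 64% | 74% |
| 10% vs 30% | 44% | 56% |
| 20% vs 35% | 74% | 80% |
| 30% vs 45% | 76% | 81% |
| 15% vs 45% | 18% | 29% |
| 20% vs 60% | 4% | 9% |

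The table is two-sided. One-sided at 42 per group, 5% vs 15% is missed 69% of the time. For 80% power at 42 per group (two-sided), a 5% reaction would have to rise to about 29% and a 10% reaction to about 37%.

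**Step 3: what the P value leaves out.** Possible results at 42 per group (treatment vs control), with the Newcombe 95% interval for the risk difference:
- 6/42 vs 2/42: Fisher P = 0.26; interval about −4 to +24 points.
- 2/42 vs 2/42: P = 1.0; interval about −12 to +12 points.
- 5/42 vs 0/42: P = 0.055; interval about +1 to +25 points.

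Working for the first upper limit: the observed proportions are 0.143 and 0.048. The Wilson upper limit for 6/42 is 0.278 and the Wilson lower limit for 2/42 is 0.013. The upper limit of the difference is 0.095 + √[(0.278 − 0.143)² + (0.048 − 0.013)²] = 0.235.

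All three results are reported as not significant. Their upper limits are about 24, 12 and 25 points, and the P value alone conveys none of this. In the third, the Newcombe interval excludes zero while Fisher's test does not reject, because the exact test is the more conservative of the two.

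**The case against.** **No wrong inference is written down.** The article says only that safety will be evaluated, that counts will be given as number (%), and that they will be tested. A reader might infer that P>.05 will be taken as proof of safety. The documents do not support that: they state no such rule and no equivalence or non-inferiority claim. This part of the objection stands in full, and the point is confined to what the stated test can and cannot deliver.

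**Missing intervals are a detail for the full protocol or SAP.** An article may leave a margin or interval method to a fuller document, and their absence is not the point here. The point is the method that section 2.9 does fix, set against an objective that the article itself names. Risk differences could be computed from the promised counts, but the article makes the test, not the estimate, its stated basis for inference.

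**Low power for adverse events is usual in trials sized on efficacy.** True, and Fisher's test is valid for sparse counts. This argues against asking for more patients, and none are asked for. It does not argue for keeping a P value as the only inferential result.

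**The rates are assumed, and the test does find large effects.** Also true. A reader might infer from the 5% vs 15% figure that any tripling would go unseen. That is not so: at 42 per group, 15% to 45% is missed about 18% of the time and 20% to 60% about 4%. Both arms receive vardenafil, and nothing in the article shows how common headache, flushing or dizziness will be. But the weakness is not confined to rare reactions either: a 15-point excess over a base of 20% or 30% is missed about three times in four.

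**Conclusion.** The point holds as a cheap improvement rather than an error in the plan. Safety is a named objective, and the one inferential method fixed for its outcome cannot state how large an excess of a reaction the trial excludes. Under assumed rates and a two-sided test, increases of 10 to 15 points are missed about 64% to 83% of the time at 42 per group across control rates of 5% to 30%, and more often at 34. Very large increases in common reactions would usually be detected.

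The size rests on the assumed rates and on the two-sided convention. A one-sided test lowers the headline miss rate from 80% to 69% and leaves the conclusion unchanged.

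**What to change.** In section 2.9, add one or two sentences on adverse reactions:
- For each named reaction, and for any reaction, report the between-group risk difference with a 95% confidence interval (Newcombe or exact) as the main safety result.
- Keep Fisher's P as a secondary result at most.
- Base the safety statement on the upper limit of the interval, and state that P>.05 will not be taken as evidence of safety.

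This uses data already planned for collection and needs no extra patients or visits. The cost is in the claim: the intervals will be wide, so the safety conclusion will be more modest.

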**Methods::**

This is a prospective randomized controlled trial to study the effectiveness and safety of bosentan combined with vardenafil in the treatment of postoperative pulmonary hypertension in children with congenital heart disease. Approved by the clinical research ethics committee of our hospital. The patients were randomly divided into 1 of 2 treatment regimens:

Patients, doctors, nurses, and data collection assistants were blinded to group allocation. Observation indicators include: oxyhemoglobin saturation (SpO2), 6-min Walking Test Distance (6 MWTD), systolic pulmonary artery pressure, mean pulmonary artery pressure, Borg score, NYHAFC score, etc. Data were analyzed using the statistical software package SPSS version 25.0 (Chicago, IL).

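### NYHA class is an ordered outcome, but the rule in section 2.9 that it most naturally falls under, Fisher's exact test, ignores the order; an ordered test would be a cheap gain in power

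*Protocol article*

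**What the plan says.** Section 2.9 sorts outcomes into two kinds. For continuous variables, "differences between groups were analyzed using a series of one-way analysis of variance (ANOVA) with Bonferroni posthoc test", with a multiway ANOVA for differences over time. For everything else, "Categorical variables were described as the number (%), and were analyzed by Fisher exact test". A P "value of <.05 was considered statistically significant". There is no separate rule for ordered categories, and no outcome is assigned to a test by name.

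NYHA appears under two labels. Section 2.7 lists it as "cardiac function classification (NYHAFC", beside the Borg score. The abstract's Methods lists "Borg score, NYHAFC score, etc".

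The sample size in section 2.3 rests on the 6-minute walk distance: "At the 5% significance level, a total of 34 patients are required for each group to achieve 90% power". No distribution, effect size or power is given for NYHA.

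**The concern.** A classification that is reported as counts and percentages belongs most naturally to the categorical rule. On a table with more than two columns, Fisher's exact test gives the same P value however the columns are permuted. It therefore treats a consistent move towards better classes like any other rearrangement of the same counts. The question for NYHA is directional: does adding bosentan improve functional class? An unordered test leaves unused the part of the data that answers this, and it gives no effect estimate.

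The two labels also lead to two different tests. Read as a score, NYHA goes to ANOVA, which keeps the order but assumes that a step from IV to III equals a step from II to I. At stake is avoidable loss of power on one of the few effectiveness outcomes named in the abstract, in a trial with 34 to 42 children per group.

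**Working it through.** **The plan's own figure.** Inputs from section 2.3: mean 495.47 (SD 54.72) in the treatment arm, and mean 456.33 (SD 54.68) in the control arm. The difference is 495.47 − 456.33 = 39.14 and the pooled SD is √((54.72² + 54.68²)/2) = 54.70. The stated formula, n = 2(u_α + u_β)²σ²/δ², at 90% power gives 33.45, so 34 per group, with a one-sided 5% critical value. With a two-sided value it gives 41.04, so 42. The stated 34 thus reproduces on the one-sided reading. Allowing for 20% withdrawal, 34/0.8 = 42.5, against 42 stated. These figures concern walk distance only. They fix the group sizes to examine (34 completing, 42 enrolled) but say nothing about power for NYHA.

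**Assumptions for NYHA.** The article supplies none, so I varied them:
- control distribution over two, three or four occupied classes
- proportional-odds shifts with odds ratio (OR) 1 to 6
- two-sided 5% level and 3,000 simulated trials per setting

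Fisher's test was the exact version for larger tables (Freeman–Halton). The comparator was the tie-corrected Wilcoxon rank-sum test.

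**How a shift is built.** For each cut k, the treated P(class ≤ k) = OR·o/(1 + OR·o), where o is the control odds of class ≤ k. With control classes I–IV of 15/40/35/10%, the cumulative proportions are 0.15, 0.55 and 0.90. At OR 3 the first becomes 3 × 0.1765/(1 + 3 × 0.1765) = 0.346, and the others 0.786 and 0.964. The treated classes are then about 35/44/18/4%. Mean class is 4 minus the sum of the three cumulative proportions: 4 − 1.60 = 2.40 in control and 4 − 2.096 = 1.90 when treated, a shift of about 0.5 class. At OR 2 the shift is about 0.3.

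**Power at 34 per group** (%; gain in points, from unrounded values):

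| Control distribution | OR | Fisher | Wilcoxon | Gain |
|---|---|---|---|---|
| 15/40/35/10 | 1.5 | 9.4 | 13.2 | 3.8 |
| | 2 | 22.2 | 34.9 | 12.7 |
| | 3 | 51.5 | 68.8 | 17.3 |
| | 4 | 70.8 | 85.7 | 14.8 |
| | 6 | 92.1 | 97.3 | 5.2 |
| 20/50/30 | 1.5 | 10.4 | 13.5 | 3.1 |
| | 2 | 23.5 | 31.2 | 7.7 |
| | 3 | 54.0 | 65.6 | 11.6 |
| | 4 | 76.8 | 85.8 | 9.0 |
| | 6 | 93.2 | 97.1 | 3.9 |
| 40/60 | 2 | 20.2 | 26.1 | 5.9 |
| | 3 | 49.4 | 57.2 | 7.8 |
| | 6 | 90.8 | 93.5 | 2.7 |

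At 42 per group and OR 3 the gains are 15.6, 11.3 and 3.5 points for the three distributions.

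**Range over all settings.** The other control distributions were 25/25/25/25, 5/25/50/20 and 30/50/15/5 (four classes) and equal thirds (three classes).
- Three or four classes, OR 2 to 4: gains of 7.7 to 18.6 points, so roughly 8 to 19.
- OR 1.5 or 6, or two classes: 2.7 to 7.8 points, so roughly 2 to 8 allowing for simulation error. The standard error of one power figure near 50% is √(0.25/3000) = 0.9 points.

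**Type I error (OR 1).** With three or four classes, Fisher 4.0 to 5.6% and Wilcoxon 4.4 to 5.2%. With two classes, Fisher 3.6 to 4.0% and Wilcoxon 5.1 to 6.3%. Two classes have no order to lose, so the gain there reflects Fisher's conservatism.

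**The ANOVA reading.** A t test on class numbers, which is one-way ANOVA with two groups, stayed within 3 points of Wilcoxon in the three- and four-class settings (67.8% against 68.8% for 15/40/35/10 at OR 3).

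**The case against.** The strongest reply is that section 2.9 never assigns NYHA to Fisher's test. That stands. The assignment is an inference from the label in section 2.7, and under the abstract's label ANOVA would keep the order and lose little power in these settings. What remains is that the two labels lead to two tests and that the more natural one is the less efficient.

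Second, the size of the loss is not a property of this trial. It depends on an assumed distribution, and proportional-odds shifts favour the Wilcoxon test. This also stands, which is why only a range is given.

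Third, Fisher's test is valid, and NYHA does not drive the sample size. Both are true and limit the severity.

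Fourth, a condensed article may leave modelling detail to an analysis plan that is not shown. That is fair for covariates and sparse-cell rules. It does not remove the point, because section 2.9 does state a rule for all categorical variables.

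A reader might also infer that every reading of section 2.9 ignores the child's class before treatment. The text does not support that: the multiway ANOVA over time could use a pre-treatment value. Nor does section 2.7 expressly say that NYHA is recorded before treatment, as it does for SpO2 and brain natriuretic peptide.

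**Conclusion.** The point holds as a cheap improvement of minor severity. On its most natural reading, section 2.9 tests an ordered effectiveness outcome with a method that ignores order. If so, and if shifts are roughly proportional-odds, the loss at 34 to 42 per group is roughly 8 to 19 points of power for moderate effects with three or four occupied classes. It is roughly 2 to 8 points for small or large effects, or with two classes. If NYHA is instead analysed by ANOVA, that loss largely disappears and the equal-spacing assumption takes its place.

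Two stronger readings are tempting and not supported. One is a single firm figure for lost power: the article gives no NYHA data from which to derive it. The other is that the trial would miss a shift of a whole class. Odds ratios of 2 to 3 move the mean by only about 0.3 to 0.5 class in the worked example. Even OR 6 moves it by less than one class (4 − 2.376 = 1.62 against 2.40, about 0.8), and there the loss is already down to about 4 to 6 points with three or four classes. Neither the validity of the trial nor the walk-distance comparison is affected.

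**What to change.** Add one sentence to section 2.9: NYHA class at month 6 is treated as ordered and compared between groups by a Wilcoxon rank-sum test, or by a proportional-odds model reporting a common odds ratio with its 95% confidence interval. Where pre-treatment class is recorded, stratify by it or adjust for it. Keep Fisher's exact test for binary items such as adverse reactions, and use one label for NYHA in the abstract and in section 2.7.

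The cost is a line of wording. The unadjusted comparison needs no new data; adjustment needs a pre-treatment class, so the protocol should confirm that it is collected. The downside of the model is its proportional-odds assumption, which the Wilcoxon test does not need in order to be valid.

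### About nine efficacy indicators are each judged at P<.05 with none named primary, and the stated Bonferroni post hoc test never corrects across indicators

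*Protocol article*

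**What the plan says.** The Abstract (Methods) gives an unranked list that begins "Observation indicators include: oxyhemoglobin saturation (SpO2), 6-min Walking Test Distance (6 MWTD), systolic pulmonary artery pressure" and is left open-ended. Section 2.7 (Observation index) gives the fuller list. Counting efficacy measures, it contains SpO2, 6MWTD, systolic pulmonary artery pressure, mean pulmonary artery pressure, the pulmonary-to-systemic flow ratio, the pulmonary-to-systemic systolic pressure ratio (Pp/Ps), brain natriuretic peptide, Borg score and NYHA class. That makes nine, or ten if aortic pressure is counted. Adverse reactions are separate. Nothing is labelled primary or secondary.

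Section 2.3 (Sample size) does single out one measure: "The calculation of the sample size is based on the results of the 6 MWTD".

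Section 2.9 (Statistical analysis) compares groups on continuous variables by "a series of one-way analysis of variance (ANOVA) with Bonferroni posthoc test". It uses multiway ANOVA, again with Bonferroni, for group differences over time, and Fisher's exact test for categorical variables. One rule covers all of these: a P "value of <.05 was considered statistically significant".

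**The concern.** Section 2.9 reads as though multiplicity has been dealt with, because a Bonferroni procedure is named. The multiplicity in this trial is across outcomes, and the named procedure works only within one outcome. With no primary outcome declared, nothing in the text ties the conclusion on effectiveness to a particular result. The trial could then be called positive on whichever indicator crosses .05, and the error rate of that conclusion would not be the nominal one.

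**Working it through.** **Reproducing the plan's own figure.** Inputs from section 2.3: for the combination arm, "the average score of the experimental group is estimated to be 495.47 and the standard deviation is 54.72". For the comparator arm, the assumed mean is 456.33 with SD 54.68. So δ = 495.47 − 456.33 = 39.14, and σ is taken as 54.70, midway between the two SDs. The stated formula is n = 2(u_α + u_β)²σ²/δ², with 2σ²/δ² = 2 × 54.70²/39.14² = 3.906.

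- One-sided 5%, 90% power: (1.645 + 1.282)² × 3.906 = 33.45, so 34 per group. This matches "At the 5% significance level, a total of 34 patients are required for each group to achieve 90% power".
- Two-sided 5%, 90% power: (1.960 + 1.282)² × 3.906 = 41.04, so 42 evaluable per group. This does not match.
- Two-sided power with 34 evaluable per group: about 84% by the normal approximation and 83% by the noncentral t.
- Withdrawal: 33.45/0.8 = 41.8, so 42, as stated. Starting from the rounded 34, 34/0.8 = 42.5, so 43, a difference of one.

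The sizing therefore concerns one test on 6MWTD and makes no allowance for other outcomes.

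**What the Bonferroni step can do.** Bonferroni multiplies each P value by the number of comparisons in the family.

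- One-way ANOVA, two arms: 2 × 1/2 = 1 comparison, so the multiplier is 1 and the P value is unchanged.
- Multiway ANOVA: section 2.6 reviews the indicators at month 6, while months 1 and 3 cover symptoms and adverse reactions. Two groups by two times give four cells, hence 4 × 3/2 = 6 possible pairwise comparisons. If those were run, Bonferroni would act, but only within that one indicator.
- Fisher's exact test: no correction is stated.

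In none of these is the number of indicators part of the family.

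**Size, if any significant indicator were accepted.** Assumptions: nine indicators, no true effect on any, each tested at two-sided .05, and normal test statistics with a common correlation ρ. The document gives no correlations, so a range is shown. At ρ = 0 the results are 1 − 0.975⁹ = 0.204 for at least one result favouring the combination and 1 − 0.95⁹ = 0.370 for either direction. For ρ > 0 they come from numerical integration over the shared component.

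| ρ | Favouring the combination | Either direction |
|---|---|---|
| 0 | 20.4% | 37.0% |
| 0.3 | 16.5% | 32.6% |
| 0.5 | 13.5% | 26.9% |
| 0.7 | 10.1% | 20.2% |
| one test only | 2.5% | 5% |

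Counting aortic pressure as a tenth indicator gives 22.4% at ρ = 0 and 14.4% at ρ = 0.5 in the favourable direction.

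**The case against.** The strongest reply is that 6MWTD is the main outcome in all but name. It alone drives the sample size, and if it decides the trial its error rate is the nominal one. The article is also condensed, and the ranking of secondary outcomes and detailed multiplicity rules are commonly left to the analysis plan. Much of this stands. The article does not treat every indicator identically, and the absence of a full multiplicity scheme is not in itself a fault. But the implication binds nobody: section 2.9 handles 6MWTD exactly as it handles Borg score or brain natriuretic peptide. The article also does describe its error control, and that description does not cover the multiplicity that matters.

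A second reply is that Bonferroni is named twice, and the multiway ANOVA clause could have an effect. That is right. A reader might infer that the Bonferroni step is inert everywhere. The text supports that only for the two-group one-way comparison. What holds for both clauses is that neither reaches across indicators.

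A third reply is that the article nowhere says one significant indicator is enough. That is also right. A reader might infer such a rule from the flat list and common threshold, but the article neither states nor excludes it.

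**Conclusion.** The point holds in limited form. No primary outcome is named although one is implied by the sizing, every indicator is judged at the same threshold, and the stated correction does not address multiplicity across indicators.

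Its size is conditional. If any significant indicator counted as evidence of effectiveness, the chance of a false result favouring the combination would be about 10% to 20% for common correlations from 0.7 down to 0, against 2.5% for one test. A reader might be tempted to quote 27% to 37% as the chance of a false claim of effectiveness. Those figures count results in either direction, including those favouring control, and assume correlations of only 0 to 0.5. Systolic pressure, mean pressure and Pp/Ps overlap closely, so higher correlations are plausible for that group. The count of nine is itself a reading of section 2.7, and the normal model is only approximate for NYHA class under Fisher's test.

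**What to change.** In sections 2.7 and 2.9:

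1. Name 6MWTD at month 6, the outcome already used for sizing, as the single primary outcome at the 5% level, and state whether the test is one- or two-sided.
2. Label all other indicators secondary, reported with 95% confidence intervals and not sufficient alone for a claim of effectiveness.
3. State that the Bonferroni post hoc test does not correct across outcomes. Drop it from the two-group ANOVA, where it has no effect. If it is kept in the multiway ANOVA, say which comparisons it covers.

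The wording is short, but there are three costs.

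- A lone significant secondary result no longer counts as proof.
- Section 2.7 measures 6MWTD only in children able to cooperate, while section 2.4 enrols from just over 6 months of age. The primary analysis population must be stated to match, and the 34 per group must be understood as children with a walking result.
- At two-sided 5%, 34 evaluable per group gives about 83% power, and 90% needs 42 evaluable. The plan says "The estimated withdrawal rate is 20%, and 42 patients will be included in each group", so 42 is the number enrolled, not the number evaluable. The power statement must be revised or the sidedness declared.

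Splitting 5% equally across nine indicators instead (0.05/9 = 0.0056 each) would cost far more. Two-sided power for 6MWTD at 34 per group would fall to about 57%, and 90% power would need 65 evaluable per group (65/0.8 = 81.25, so 82 enrolled). Naming one primary outcome avoids that.
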